### Study endpoints and statistical analyses

The primary endpoint is defined as the difference in mean total cerebral microemboli count during the measurement period on CRRT versus IRRT following randomization.

Secondary endpoints include:Increase in cerebral microemboli count and rate (= count/RRT minute) in the middle cerebral artery in CRRT (CRRT group) versus IRRT (IRRT group) in relation to the baseline measurement in both groups during CRRTIncrease in microbubble count and rate (= count/RRT minute) in the venous outflow of the RRT circuit in CRRT (CRRT group) versus IRRT (IRRT group) in relation to the baseline measurement in both groups during CRRTRelationship between the counts/rates of microbubbles and cerebral microemboliVolume and number of new ischemic lesions on periprocedural MRI and their correlation to cerebral microembolic load/microbubble countICU mortality, in-hospital and 30-day mortality, intensive care unit length of stay, total hospital length of stay, days on RRTRelation of the findings to underlying reason for AKI/need for RRT (descriptive analysis)Relation of the findings with regard to hemodynamic data, if available (heart rate, systolic blood pressure, diastolic blood pressure, central venous pressure, vasopressor usage)

The primary endpoint results from the difference in mean total cerebral microemboli count in CRRT versus IRRT recipients compared with analysis of covariance (ANCOVA). To assess relationships between cerebral microemboli/microbubble count and the number of ischemic lesions on MRI, the Pearson correlation coefficient will be used. Other parameters will be analyzed in a descriptive fashion with parametric or non-parametric statistical methods. A significance level of 0.05 will be considered.

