### Study population and patient allocation

Consecutive critically ill patients treated with CRRT for AKI, and scheduled to be switched (as determined by the treating ICU physician in charge) to IRRT, will be randomized by an independent computer-based procedure to either switch to IRRT the next day or to continued CRRT for one additional day. Doppler measurements will be performed during CRRT for both groups before the switch (baseline, examination day 1) and after the switch (follow-up measurement, examination day 2) in the CRRT and IRRT groups, respectively. In the IRRT group, there will be a RRT pause of 12 h between CRRT termination and IRRT start in order to allow equilibration and wash out of potential CRRT-induced microemboli. Transcranial Doppler (TCD) detection of cerebral microemboli will be performed bilaterally and continuously in both middle cerebral arteries (MCAs) for 30 min. Additionally, microbubble generation will be simultaneously recorded in the RRT circuit by extracorporeal Doppler detector in the venous tubing, placed 10 cm downstream of the air detector (Fig. 1). No interventions (e.g., bolus intravenously administered (IV) drug injections, line flushing, change of infusion rate, blood sampling or other manipulations) will be allowed during Doppler examinations. At the beginning and at the end of the study period, patients will undergo routine clinical examinations to evaluate for neurological and neurocognitive disturbances. A magnetic resonance imaging (MRI) examination will be performed after inclusion of the patient in the study and again after completion of the follow-up Doppler measurements (Fig. 2).

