### Sample size calculation

Based on our preliminary study, [19] we expect a true difference in the mean high-intensity transient signals (HITS) value of 700 and a standard deviation of 950 HITS between the two groups of interest. With a desired power of 0.8 and an alpha of 0.05, the number of required patients is 58 (29/group). Taking into consideration a dropout rate of 15%, we plan to include a total number of patients of 66.

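### The increases in circuit microbubbles and cerebral microemboli read as unadjusted change scores; the plan should say that the pre-randomisation baseline enters the comparison as a covariate (minor).

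*Protocol article*

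**What the plan says.** All of this is in the protocol article.

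- **Cerebral endpoint** (Study endpoints and statistical analyses, first secondary endpoint): "Increase in cerebral microemboli count and rate (= count/RRT minute) in the middle cerebral artery in CRRT (CRRT group) versus IRRT (IRRT group"), taken relative to the baseline on CRRT.
- **Circuit endpoint** (same section, second secondary endpoint): the increase in microbubble count and rate "in the venous outflow of the RRT circuit in CRRT (CRRT group) versus IRRT (IRRT group) in relation to the baseline measurement".
- **Primary analysis** (same section): "The primary endpoint results from the difference in mean total cerebral microemboli count in CRRT versus IRRT recipients compared with analysis of covariance (ANCOVA"). The covariates are not named.
- **Everything else**, apart from the Pearson correlations with MRI lesions: "Other parameters will be analyzed in a descriptive fashion with parametric or non-parametric statistical methods". A significance level of 0.05 follows.
- **Baseline** (Study population and patient allocation): "Doppler measurements will be performed during CRRT for both groups before the switch (baseline, examination day 1"). Study periods and visits puts this recording at Visit 3 and randomisation at Visit 4, at the end of the same day.

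**The concern.** Two endpoints are expressed as an increase and compared between arms, and the one covariate-adjusted method in the section is tied to a different endpoint. Read plainly, the increases would be compared by a two-sample test or interval that does not use baseline as a covariate. Such a comparison carries the noise of both recordings. With equal SDs and a correlation below 0.5, it is even less precise than ignoring the baseline.

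The circuit endpoint has most at stake. The primary objective in Methods/design takes in bubble formation as well as cerebral emboli, and the hypothesis in Background starts in the circuit. The primary endpoint measures only the cerebral count, so the secondary circuit endpoint is the only between-arm comparison of bubble formation. An unadjusted comparison could give a wider interval than the data require. It would also correct a chance baseline imbalance by too much or too little.

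**Working it through.** **Inputs from the document** (Sample size calculation): "we expect a true difference in the mean high-intensity transient signals (HITS) value of 700"; "a standard deviation of 950 HITS between the two groups of interest"; "With a desired power of 0.8 and an alpha of 0.05"; 29 per group. The text does not say whether 950 is the SD of a follow-up count or of a change.

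**Inputs assumed:** the baseline-to-follow-up correlation r, and k, the baseline SD divided by the follow-up SD. The document gives neither.

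**1. The plan's own figure.** n per arm = 2 × (1.960 + 0.842)² × 950² / 700² = 28.9, which rounds up to 29, or 58 in total. The stated figure reproduces with a two-sided 5% level and the normal approximation. With the t distribution, power at 29 per arm is 0.787.

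**2. Variances.** Let s be the follow-up SD.
- Unadjusted change: s²(1 + k² − 2kr)
- ANCOVA: s²(1 − r²)
- Difference: s²(k − r)²

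The change score is therefore never more precise than ANCOVA, apart from the degree of freedom in step 5, and the two are equal where k = r.

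**3. Equal SDs (k = 1).** The ratio of ANCOVA to change variance is (1 − r²) / [2(1 − r)] = (1 + r)/2.

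| r | Change / s² | ANCOVA / s² | Ratio |
|---|---|---|---|
| 0.2 | 1.60 | 0.96 | 0.60 |
| 0.5 | 1.00 | 0.75 | 0.75 |
| 0.7 | 0.60 | 0.51 | 0.85 |

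**4. Unequal SDs.**
- k = 0.75, r = 0.2: change 1 + 0.5625 − 0.30 = 1.2625; ratio 0.96/1.2625 = 0.76, a gain of 24%.
- k = 0.5, r = 0.5: change 1 + 0.25 − 0.50 = 0.75; ratio 0.75/0.75 = 1.00, no gain.
- k = 1.25, r = 0.2: change 1 + 1.5625 − 0.50 = 2.0625; ratio 0.96/2.0625 = 0.47.

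The change score is less precise than the follow-up value alone when r is below k/2. That threshold is 0.5 only if the SDs are equal.

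**5. Cost of the covariate.** One residual degree of freedom. With 58 patients the variance inflation is about 1 + 1/(58 − 4) = 1.019.

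**6. Does the increase scale itself lose precision?** If the follow-up value is modelled as a + τ·arm + b·baseline, the increase is a + τ·arm + (b − 1)·baseline. Only the baseline slope changes. A simulated set of 58 patients confirms it: the effect is 0.877 with SE 0.192 whether follow-up or increase is the outcome, against 0.839 with SE 0.208 for the unadjusted increase.

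**7. Illustration only.** This borrows 700/950 from the cerebral primary endpoint, treats 950 as the SD at both times, and uses 29 per arm. Power is t-based, with the covariate cost charged; n per arm is for 80% power by the normal approximation.

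| r | Power, change | Power, ANCOVA | n per arm, change | n per arm, ANCOVA |
|---|---|---|---|---|
| 0.2 | 0.587 | 0.796 | 47 | 28 |
| 0.5 | 0.787 | 0.884 | 29 | 22 |
| 0.7 | 0.945 | 0.969 | 18 | 15 |

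**The case against.** The strongest reply is that the article fixes the scale of the endpoint, not an unadjusted test. It prescribes no change-score comparison and does not exclude a covariate. The model for a secondary endpoint is commonly left to an analysis plan, which is not shown. This stands in part: a reader might infer that the protocol commits to an unadjusted analysis, or that calling the endpoint an increase gives up precision. The first is only the plain reading of the section, and step 6 shows the second to be wrong.

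Three further replies stand.
- The primary ANCOVA already compares the follow-up cerebral count. If baseline is its covariate, the cerebral half is largely settled: recording is planned for 30 minutes, so for a full recording the rate is only a rescaled count.
- The secondary endpoints are descriptive and unpowered. The 0.05 level leaves room for testing, but no sample size or decision rule rests on them.
- Equal SDs cannot be taken for granted. Every baseline is on CRRT at 150 ml/min and IRRT runs at 300 ml/min, so follow-up counts could well vary more.

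A reader might also take the power figures as the trial's own loss of power. The document does not support that: it gives no effect size or SD for circuit microbubbles.

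The reply does not remove the point that the section assigns adjustment to one endpoint and a looser method to the rest. That division leaves the circuit comparison without the adjustment that the design makes available.

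**Conclusion.** The point holds as a minor one. Read plainly, the two increases would be compared without baseline adjustment, and the baseline is a valid covariate because it is recorded before randomisation. With equal SDs the saving in variance is 40%, 25% and 15% at assumed r of 0.2, 0.5 and 0.7. It shrinks as the SD ratio falls towards r, and vanishes where they are equal. The result rests on a linear adjustment with a common slope in both arms; skewed counts may need a transformation or a count model. The circuit endpoint is the stronger case. No figure stated in the plan is wrong on this account.

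**What to change.** Add one sentence to Study endpoints and statistical analyses. It should say that the between-arm comparison of circuit microbubble count and rate will include the patient's own Visit 3 value as covariate, on a scale suited to counts, and will report the adjusted difference with its 95% CI. The same should apply to the cerebral count and rate wherever the primary ANCOVA does not already do this. If the analysis plan already says so, a reference to it is enough.

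The endpoints may still be labelled increases. In a linear model the treatment effect and its SE are identical, provided that the increase and the covariate are on the same scale.

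The cost is one residual degree of freedom. No new data are needed, and the planned sample size is unaffected.

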### Study devices and neurocognitive examinations

Renal replacement therapyContinuous renal replacement therapy is provided by PrismaflexTM (Gambro Hospal GmbH, [name]). Intermittent renal replacement therapy is provided by Dialog + (B Braun Melsungen, AG, [name]). CRRT will be performed as follows: continuous veno-venous hemodialysis and filtration (CVVHDF) applied daily for 24 h (target) using a poly-sulfone synthetic membrane and bicarbonate-buffered substitution fluids (blood flow 150 ml/min, dialysate flow 1000 ml/h, substitute 500 ml/h, if applicable: pre-pump substitute containing citrate 1500 ml/h). Regional citrate anticoagulation (at a citrate dose of 3 mmol/l) will be used as standard anticoagulant. A delivered CRRT “dose” of > 30 ml/kg body weight/h applies. IRRT will be performed for 4 h using volumetric ultrafiltration control, water purified by reverse osmosis and bicarbonate-buffered dialysate. Blood flow and dialysate flow will be kept at 300 ml/min and 500 ml/min, respectivelyDoppler measurementsCerebral microemboli detection will be performed with TCD (Delica 9UA series, Delica, Shenzen, China), which is equipped with a 1.6-MHz robotic transducer and a commercially available computer. The TCD probes will be mounted bilaterally over the temporal bone window using a dedicated size-adjustable probe-holder. HITS will be detected using the current version of EDS software (SMT medical, Wurzburg, Germany). TCD measurements will be performed according to the guidelines established by the International Consensus Group on Microembolus Detection. The MCA will be automatically insonated by the robotic TCD probes, and the Doppler velocity spectral range will be adapted to the expected maximum MCA flow velocity. Power output and gain settings will be adjusted to provide an optimal signal-to-noise ratio. On the basis of neural network technology, the EDS software automatically classifies every intensity increase within the Doppler spectrum as a cerebral microembolus (solid or gaseous) or as an artefact. After microemboli detection is complete, two experts, blinded to the study groups, will review all recordings off-line in order to confirm correct signal detection and differentiation. Microbubble detection in the RRT circuit is performed using the CMD-20 1.5-MHz ultrasound detector (Hatteland Instrumentering, Røyken, Norway) connected to the venous tubing and placed 10 cm downstream to the air detector. The device is a microbubble detector specifically designed for extracorporeal lines with an operation principle based on the pulsed Doppler technique; when the ultrasonic pulse hits a microbubble in the extracorporeal line the pulse will be partially reflected to the probe but with a different frequency than the transmitted wave (Doppler shift). The amplitude of the Doppler shift is proportional to microbubble diameter which allows for the possibility to classify both the size and the count of each microbubble passing the tubeMagnetic resonance imagingImaging studies are performed on either a 1.5-T or a 3-T Siemens MRI system (Magnetom Avanto, Magnetom Trio; Siemens Medical Solution, Erlangen, Germany) with a 12-channel coil.The MRI protocol encompasses a routine MRI protocol with following sequences: axial diffusion-weighted imaging (DWI), axial fluid-attenuated inversion recovery (FLAIR), susceptibility-weighted imaging (SWI), time-of-flight (ToF) angiography and axial T1wSE post contrastNeurocognitive examinationTo access neurocognitive and health disturbances, patients are subjected to a battery of tests: (1) Confusion Assessment Method for the Intensive Care Unit (CAM-ICU), (2) Richmond Agitation and Sedation Scale (RASS), (3) Montreal Cognitive Assessment (MoCA) and (4) the Short Form (36) Health Survey (SF-36)

### Severe adverse events and safety

Severe adverse events are assessed by the PI and are Medical Dictionary for Regulatory Activities (MedDRA)-coded in the Case Report Form (CRF) during the clinical phase and the follow-up period. All adverse events will be reported to the CEC in accordance with all national and institutional requirements.

### Quality assurance and control

Study data are recorded manually on the paper CRF (p-CRF) and entered after completion of the measurements in each participant into an electronic data base (double data entry). For each enrolled study participant, a CRF is maintained. CRFs are kept current to reflect subject status at each phase during the course of study. Participants cannot be identified in the CRF by name, initials and/or birth date. Appropriate coded identification with participant number in combination with date of the investigation (year, month, day) is used. Authorization for CRF entries is provided on the form “*Staff education, roles, responsibilities and signatures*” submitted as a unique document to the CEC.

### Specification of source documents

Source data include original documents relating to the study, as well as the medical treatment and medical history of the participant. All documents containing measurements (e.g., CRF) or other patient-related data (e.g. demographic data, visit dates, participation in study and Informed Consent Forms, randomization number, serious adverse events, and concomitant medication, results of relevant examinations) are considered source documents.

### Record keeping/archiving

All study data will be archived for a minimum of 10 years after study termination or premature termination of the clinical trial.

### Data management

At the departmental research platform, three locally separated dedicated servers are installed for research data management. The servers are running on Windows Server and using SQL Server (Microsoft Corporation, [name]) for the relational data base. The web application LabKey Server is implemented in Java and is running on the Apache Tomcat web server. The data are stored in relational data base engines such as PostgreSQL or Microsoft SQL server.

### Data security, access and backup

LabKey Server provides web application security and can be configured for Secure Socket Layer (SSL)-encrypted data transfer. The application has a group and role-based security model. Each user belongs to one or more security groups with specific sets of permissions in relation to folder or projects in the system. Only dedicated site administrators have access to the administration console enabling user management and changing security settings. Data are stored and visualized in data grids either in the format of datasets, lists or assays. Each change of data is tracked and documented in corresponding audit log files. The system can only be accessed entering a user name and password. All events are recorded in the user event list of the audit log files.

The application is running on a productive server with an image on a backup server. In addition, a regularly backup of the whole data base is implemented using storage servers.

### Analysis and archiving

LabKey Server provides data analysis by integrated tools for creating filtered views and charts. All data can be exported in different formats (Excel, text, queries) suitable for transfer to a statistical software package of choice. In addition, data can be analyzed creating R views. All data will be archived and secured in the data base as long as required by legislation.

### Electronic and central data validation

Data validity will be controlled by cross-checking the p-CRFs and the electronic data bases.

### Dissemination policy

We plan to publish the data in a peer-reviewed, high-ranking clinical journal.

## Discussion

The cerebral microembolic burden during RRT may represent an underestimated problem that can contribute to neurological complications and adverse clinical outcomes. Associated repeated hospital stays and outpatient follow-ups can be considered potential additional factors leading to an increase in healthcare costs. We expect that COMET-AKI provides more detailed insight in RRT modality-associated differences with regard to microbubble generation and cerebral microembolic burden.

Currently, it seems generally accepted by physicians and manufacturers that microbubbles are generated within the RRT circuit and that some bubbles may enter the patient’s cerebral circulation during RRT sessions. With no apparent immediate clinical side effects for RRT-treated patients, the problem of microbubbles in RRT patients appears currently not within the scope of interest. If a significant number of microbubbles would indeed be detected within the systemic circulation of the patient (i.e., in the cerebral vessels), the potential problem of microbubbles in RRT recipients may become even more significant. Our data may further provide the scientific basis for longitudinal studies relating cerebral microbubbles to changes in cognitive functions. Furthermore, identification of covariates of bubble formation and distribution may help to encourage the evolution of next-generation RRT circuits, machinery, and/or filters with reduced microbubble generation and distribution (Additional file 1).

### Trial status

Recruitment started in October 2016 and is estimated to be completed in October 2018.

## Abbreviations

AKI: Acute kidney injury
ANCOVA: Analysis of covariance
APACHE: Acute Physiology And Chronic Health Evaluation
CAM-ICU: Confusion Assessment Method for the Intensive Care Unit
CEC: Cantonal Ethics Committee
CONSORT: Consolidated Standards of Reporting Trials
CRF: Case Report Form
CRRT: Continuous renal replacement therapy
CVVHDF: Continuous veno-venous hemodialysis and filtration
DWI: Diffusion-weighted imaging
FLAIR: Fluid-attenuated inversion recovery
GCP: Good Clinical Practice
HITS: High-intensity transient signals
ICH: International Council on Harmonization
ICU: Intensive care unit
IRRT: Intermittent renal replacement therapy
MCA: Middle cerebral artery
MedDRA: Medical Dictionary for Regulatory Activities
MoCA: Montreal Cognitive Assessment
MRI: Magnetic resonance imaging
PI: Principal investigator
RASS: Richmond Agitation and Sedation Scale
RRT: Renal replacement therapy
SAPS: Simplified Acute Physiology Score
SF-36: Short Form Health Survey
SOFA: Sequential Organ Failure Assessment Score
SWI: Susceptibility-weighted imaging
TCD: Transcranial Doppler ultrasound
TISS: Therapeutic Intervention Scoring System
